### Intervention Procedures

Both procedures will be performed under peribulbar anesthesia using a standardized phacoemulsification technique.

For group A, a retropupillary iris-claw IOL will be implanted using standard enclavation of haptics onto the posterior iris surface after thorough anterior vitrectomy. For group B, a single-piece foldable IOL will be fixated with 10‐0 polypropylene (Prolene) sutures passed through partial-thickness scleral flaps created at the 3- and 9-o’clock positions, ensuring equal centration. All surgeries will adhere to uniform intraoperative and postoperative protocols, including the use of balanced salt solution, intracameral antibiotics, and a topical steroid–antibiotic combination therapy postsurgery. To ensure reproducibility, procedural videos will be periodically reviewed by the data monitoring committee for intersurgeon standardization.

### Timeline of Assessments

The schedule of preoperative, intraoperative, and postoperative assessments is outlined in Table 1.

**Table 1. T1:** Timeline of clinical assessments and outcome measures.

Study phase	Assessment parameters
Preoperative	Visual acuity (Snellen’s chart), slit-lamp biomicroscopy, intraocular pressure (NCT^a^), fundus evaluation, and biometry (A-scan, keratometry)
Day 0 (surgery)	Type of IOL^b^ fixation, intraoperative complications, surgical duration, and intraoperative stability
Day 1	Corneal clarity, anterior chamber reaction, intraocular pressure, and early complications
Day 15	BCVA^c^, astigmatism (autorefractometry), anterior chamber reaction, and IOL position
Day 30	BCVA, lens centration/tilt (slit-lamp retroillumination as per Calzetti et al [10]), intraocular pressure, and patient comfort
Day 90	Final BCVA, lens-induced astigmatism, postoperative complications, and patient satisfaction (NEI VFQ-25^d^)

a NCT: noncontact tonometry.

b IOL: intraocular lens.

c BCVA: best-corrected visual acuity.

d NEI VFQ-25: National Eye Institute Visual Function Questionnaire-25.

### Outcome Measures

Primary outcomes:

BCVA at 3 months using Snellen’s chart, converted to logMAR values for statistical analysis.Lens-induced astigmatism, measured through keratometry and autorefractometry.

Secondary outcomes:

Intraoperative complications (posterior capsular rupture extension, vitreous loss, surgical duration).Postoperative complications (hyphema, pigment dispersion, raised intraocular pressure, IOL decentration, cystoid macular edema).IOL centration and tilt, assessed by slit-lamp retroillumination following the method of Calzetti et al [10].Patient-reported satisfaction and visual function, measured using the National Eye Institute Visual Function Questionnaire-25 at 3 months.

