**Methods:**

This is a prospective, 2-arm, open-label randomized controlled trial being conducted at the Department of Ophthalmology, Acharya Vinoba Bhave Rural Hospital, Sawangi, India. A total of 92 patients aged 35 to 75 years with intraoperative posterior capsular compromise will be randomized (block randomization, sealed opaque envelopes) into 2 groups: group A (retropupillary iris-claw IOL) and group B (scleral-sutured IOL). Preoperative, intraoperative, and postoperative data will be collected at day 1, day 15, day 30, and day 90. The primary outcomes are best-corrected visual acuity and lens-induced astigmatism at 3 months. Secondary outcomes include IOL centration or tilt, intraoperative and postoperative complications, and patient satisfaction (assessed using the National Eye Institute Visual Function Questionnaire-25). Data will be analyzed using ANOVA and mixed-effects models.

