**Conclusions:**

This randomized protocol is designed to generate comparative clinical evidence on the efficacy, safety, and visual stability of iris-claw and scleral-sutured IOL fixation in primary cataract surgery. The findings will contribute to optimizing surgical decision-making in cases with deficient posterior capsular support.

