## Introduction

### Overview

Cataract remains the leading cause of reversible blindness worldwide and continues to impose a major public health burden, particularly among older adults in low- and middle-income countries [1]. In 2020, an estimated 79 million individuals aged 50 years and older were affected globally, representing a 39% increase in prevalence since 1993 [2]. The only definitive treatment is surgical extraction of the opacified lens followed by intraocular lens (IOL) implantation [3]. Phacoemulsification with posterior chamber IOL placement is the preferred modern technique due to its faster recovery, smaller incision size, and superior visual outcomes [4]. However, intraoperative or pre-existing capsular rupture can complicate surgery and preclude standard posterior chamber fixation, resulting in aphakia and unstable visual rehabilitation [3,5].

When the posterior capsule is compromised, secondary fixation techniques are required to achieve optical stability. The 2 widely practiced approaches are retropupillary iris-claw IOL fixation and scleral-sutured posterior chamber IOL fixation [6]. In iris-claw implantation, the lens is enclavated onto the midperipheral iris, providing a relatively simple and reproducible procedure with shorter operative time [5]. Conversely, scleral-sutured fixation secures the IOL haptics within scleral flaps using 10‐0 polypropylene (Prolene; Ethicon) sutures, offering stable posterior chamber positioning and a reduced risk of endothelial trauma but requiring greater surgical expertise [7]. Both techniques have evolved substantially, yet each carries distinct risks, such as iris chafing, pupil distortion, or suture degradation [8,9].

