### Hypothesis

This randomized controlled trial hypothesizes that retropupillary iris-claw IOL implantation will achieve visual outcomes (measured by best-corrected visual acuity [BCVA] and lens-induced astigmatism at 3 months) that are noninferior or superior to those obtained with scleral-sutured fixation. It is further hypothesized that the iris-claw technique will demonstrate shorter operative time and fewer intraoperative and postoperative complications, while maintaining comparable centration and patient-reported satisfaction scores.

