## Discussion

Management of aphakia during cataract surgery remains a critical surgical challenge, particularly when posterior capsular rupture or zonular instability precludes in-the-bag IOL implantation [11,12]. Although several fixation techniques have been developed, the comparative efficacy and safety of scleral-sutured and retropupillary iris-claw fixation during primary cataract surgery remain insufficiently explored [13]. This protocol aims to prospectively evaluate these two commonly used methods under standardized conditions. The rationale for comparing scleral-sutured and iris-claw fixation stems from their distinct anatomical and procedural advantages. Retropupillary iris-claw lenses offer a posterior chamber position similar to that of an in-the-bag IOL while avoiding contact with the corneal endothelium and anterior chamber angle [2,3]. They are relatively simple to implant, require shorter surgical time, and provide satisfactory centration with minimal postoperative astigmatism [5,7]. Conversely, scleral-sutured fixation restores a near-physiological IOL position behind the iris plane and has been associated with excellent visual outcomes and long-term stability [8]. However, it demands greater surgical skill and carries the potential of suture-related complications, including knot erosion and late dislocation [14,15].

Several retrospective and comparative studies have examined the outcomes of these techniques, but most involve heterogeneous populations or secondary IOL implantations. Madhivanan et al [5] demonstrated that both retropupillary iris-claw and scleral-fixated IOLs achieve significant improvement in BCVA, although scleral fixation required longer surgical duration. Similarly, Durmus et al [7] reported comparable visual outcomes but found that endothelial cell loss was lower with iris-claw lenses than with sutureless scleral fixation. Shahid et al [8] emphasized that scleral fixation provides superior long-term centration yet remains technically demanding and time-intensive. These findings justify the need for a prospective, randomized evaluation focusing specifically on primary cataract cases rather than secondary or complicated aphakia.

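### The postoperative complication outcome omits pupil distortion, suture degradation and knot erosion, which the protocol itself names as risks of these techniques, so the hypothesis of fewer complications would be tested on an incomplete list

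*Protocol article*

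**What the plan says.** **Risks named.** The Overview says of the two techniques that "each carries distinct risks, such as iris chafing, pupil distortion, or suture degradation". The Discussion adds that scleral-sutured fixation "carries the potential of suture-related complications, including knot erosion and late dislocation".

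**Hypothesis.** The Hypothesis section is directional. It expects that "the iris-claw technique will demonstrate shorter operative time and fewer intraoperative and postoperative complications".

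**Outcome.** Outcome Measures defines the secondary outcome as "Postoperative complications (hyphema, pigment dispersion, raised intraocular pressure, IOL decentration, cystoid macular edema". IOL centration and tilt form a separate secondary outcome.

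**Capture and timing.** Adverse Event Reporting and Monitoring requires every adverse event to be documented at each follow-up. The abstract's Methods state that "postoperative data will be collected at day 1, day 15, day 30, and day 90". The Day 90 row of Table 1 reads "Final BCVA, lens-induced astigmatism, postoperative complications, and patient satisfaction".

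**Analysis and conclusion.** Data Management and Statistical Analysis compares categorical variables, with complications as an example, by the chi-square or Fisher exact test at P<.05. The abstract's Conclusions say that the trial is to yield "comparative clinical evidence on the efficacy, safety, and visual stability of iris-claw and scleral-sutured IOL fixation", with no time limit in that sentence.

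**The concern.** A comparison of complications informs the choice between two techniques only if it counts the harms in which they are expected to differ. The article names such harms when it motivates the trial, then leaves three of them out of the outcome that is to be compared. Followed as written, an eye with a distorted pupil, or one with an eroded knot or degraded suture, has no postoperative complication for this outcome unless it also has one of the five listed events. A finding of fewer complications with the iris-claw lens, or of no difference, could then depend partly on which items were listed.

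Timing is a lesser matter. The Discussion itself calls dislocation late, and follow-up ends at Day 90. Safety statements from this trial therefore concern early events, and neither the abstract's Conclusions nor the complication hypothesis says so.

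**Working it through.** **Step 1: set the named risks against the outcome.** Named risks come from the Overview and Discussion. Coverage comes from Outcome Measures and Table 1.

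| Risk named | In the five-item list? | Elsewhere among outcomes or in Table 1? |
|---|---|---|
| Iris chafing | Not by name; pigment dispersion is the nearest item | No |
| Pupil distortion | No | No |
| Suture degradation | No | No |
| Knot erosion | No | No |
| Late dislocation | In part, as IOL decentration | In part: IOL position at Day 15, centration/tilt at Day 30 and as a secondary outcome |

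Three risks are wholly absent and one is partly covered. Reoperation on the lens is not listed either.

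**Step 2: is the list closed?** The items stand in parentheses with no word marking them as examples. The article does mark examples elsewhere: the Overview's list of risks is introduced as examples, and the statistical section uses eg. The natural reading is that the five items are the outcome.

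**Step 3: do adverse events fill the gap?** They do for recording. For the comparison, the adverse-event section provides for ethics committee reporting and data monitoring review. Neither it, Outcome Measures nor the statistical section says that recorded adverse events become part of the complication outcome.

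**Step 4: which way could the result move?** The documents give no event rates, so every rate here is an assumption. Let listed events occur in 20% of both arms. Let omitted harms occur independently at rate a in group A (iris-claw) and b in group B (scleral-sutured). The rate of any complication is then 1 - 0.8(1 - a) in A and 1 - 0.8(1 - b) in B, so the difference A - B is 0.8(a - b).

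| a | b | Difference on the list | Difference with omitted harms |
|---|---|---|---|
| 0 | 0.20 | 0 | -16 points |
| 0 | 0.10 | 0 | -8 points |
| 0.10 | 0.10 | 0 | 0 |
| 0.10 | 0 | 0 | +8 points |
| 0.20 | 0 | 0 | +16 points |

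The sign depends on a - b, which the documents do not give.

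**Step 5: how few eyes matter?** With 92 patients allocated 1:1 there are 92/2 = 46 per arm. A 10% rate of an unlisted harm is 0.10 × 46 = 4.6 eyes. Two-sided Fisher exact tests on invented counts of eyes with any complication:

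| Iris-claw | Scleral-sutured | P |
|---|---|---|
| 5/46 | 14/46 | .038 |
| 9/46 (four more eyes with only pupil distortion) | 14/46 | .34 |
| 5/46 | 9/46 | .38 |
| 5/46 | 14/46 (five more eyes with only suture or knot harm) | .038 |
| 6/46 | 14/46 | .075 |

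Four or five uncounted eyes can erase or create significance. The last row shows that the example sits at the threshold, where a single further event also changes the reading. The example assumes a pooled any-complication variable, which the article does not define.

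**The case against.** **The harms are recorded anyway.** This stands as to capture: all adverse events are documented at each follow-up, and Table 1 uses unrestricted wording for complications at Day 1 and Day 90. It does not settle what is compared. If recorded events are to count, the rule for counting them should be fixed before the data are seen, particularly as surgeons and patients are unblinded.

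**The article condenses a fuller protocol, and a complication checklist may sit in the case report form.** That is possible, and nothing in the article says that only these five items count. But the article does not defer the definition elsewhere. It states a list, and that list does not match its own account of the risks.

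**No pooled endpoint is defined.** This stands. If each type is compared separately, an omitted harm cannot alter the result for a listed one. The numerical example is therefore only an illustration. The omitted harms would still have no place in the comparison.

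**A reader might infer that the list is lopsided, favoring one arm.** The documents do not support this. The list has an iris-related item (pigment dispersion) and no suture-specific one, but it also lacks pupil distortion. Harms are missing on both sides, and the Overview does not assign its examples to arms.

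**A reader might also infer that dislocation is ignored, or that Day 90 is a design error.** Neither holds. Decentration, IOL position and centration/tilt cover displacement in part. Day 90 is a disclosed choice that matches the 3-month primary outcomes. There is also some tension in arguing that suture harms arise late and yet assuming an appreciable rate of them by Day 90. If they are mainly late, adding them changes the 90-day comparison little, and the time limit on the conclusion matters more.

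**Conclusion.** The point holds as a gap in the definition of a secondary outcome. Three risks that the article names (pupil distortion, suture degradation and knot erosion) are absent from the complication list, dislocation is only partly covered, and no link brings recorded adverse events into the comparison between arms. A directional hypothesis and a stated safety aim rest on that outcome, so it should be corrected, although the primary outcomes are untouched.

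Neither the direction nor the size of any bias can be found from the documents. The range of -16 to +16 points and the P values depend on assumed rates, invented counts and a pooled variable. They show only that a few eyes among 46 per arm could matter. The reading of the list as closed rests on its wording. On follow-up, only a 3-month qualifier is called for.

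**What to change.** - **Outcome Measures:** add pupil distortion; suture or knot exposure, erosion or breakage; IOL dislocation or haptic disenclavation; and any reoperation on the lens.
- **Table 1:** have these checked in both arms at the existing postoperative visits (Days 1, 15, 30 and 90).
- **Reporting:** give each complication type by arm, beside any pooled count.
- **Hypothesis and the abstract's Conclusions:** state that the complication and safety conclusions cover 3 months only.

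The cost is a few more case report form fields at visits already scheduled, slightly more data entry, and a narrower conclusion. No extra visit is needed.

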### Data Management and Statistical Analysis

Statistical methods used for data management and analysis are summarized in this section. Continuous variables (eg, BCVA, astigmatism, and intraocular pressure) will be summarized as mean (SD) and analyzed using the independent *t* test for between-group comparisons and repeated-measures ANOVA for longitudinal analysis. Categorical variables (eg, complications and sex) will be compared using the chi-square test or the Fisher exact test. Multivariate analysis will be performed using mixed-effects linear regression to adjust for baseline covariates (age and preoperative vision). Missing data will be handled using multiple imputation under a missing-at-random assumption. Interim analysis will be conducted after 50% enrollment to evaluate safety and adherence; no stopping rules for efficacy are planned. Statistical analyses will be performed using SPSS software (version 27.0; IBM Corp). A *P* value <.05 will be considered statistically significant.

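### The NEI VFQ-25 is reported as patient satisfaction though it is by name a visual function score, its Day 90 comparison names no fellow-eye covariate, and comparable scores are hypothesized without a margin

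*Protocol article*

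**What the plan says.** All references are to the protocol article.

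- **Outcome Measures** lists among the secondary outcomes "Patient-reported satisfaction and visual function, measured using the National Eye Institute Visual Function Questionnaire-25 at 3 months". One score serves two constructs.
- **Timeline of Assessments, Table 1** lists for Day 90 "Final BCVA, lens-induced astigmatism, postoperative complications, and patient satisfaction", with the NEI VFQ-25 in brackets after the last item. The preoperative row begins "Visual acuity (Snellen’s chart), slit-lamp biomicroscopy, intraocular pressure" and contains no questionnaire. It does not say which eye or eyes are tested.
- **Abstract, Methods** says "Secondary outcomes include IOL centration or tilt, intraoperative and postoperative complications, and patient satisfaction", again with the NEI VFQ-25 as the measure.
- **Hypothesis** expects fewer complications and shorter surgery with the iris-claw lens, "while maintaining comparable centration and patient-reported satisfaction scores".
- **Data Management and Statistical Analysis** gives the independent t test for between-group comparisons of continuous variables, significance at P<.05, and "mixed-effects linear regression to adjust for baseline covariates (age and preoperative vision" in brackets. It states no margin for the questionnaire score and names no fellow-eye measure.

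**The concern.** There are three linked problems.

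1. **The label.** Satisfaction and visual function are different constructs. A patient may function well and be dissatisfied, or the reverse. The plan as written leads to a published statement about satisfaction from an instrument whose name says it measures visual function.

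2. **The unit.** The trial compares two ways of fixing a lens in one eye. A questionnaire answered by a person reflects the vision that person has, which includes the other eye. The eligibility criteria do not restrict fellow-eye lens status, so that eye may be clear, already operated or cataractous. Differences between patients in that eye add noise to the score, and a good fellow eye can mask part of what happens in the study eye.

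3. **The conclusion sought.** The hypothesis expects comparable scores, but the analysis offers a test for a difference. With a diluted and noisy score, a nonsignificant result is likely whether or not the techniques differ, and it would read as confirmation.

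**Working it through.** **Inputs.** The abstract gives 92 patients and the randomization section gives 1:1 allocation, so 92 / 2 = 46 per arm. Alpha is 0.05, taken as two-sided because the article does not say. The sample size derivation is in Multimedia Appendix 1, which is not at hand, so 92 cannot be reproduced. The article gives no SD, correlation or margin for the NEI VFQ-25. Every such value below is an assumption.

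**1. Is the Day 90 contrast valid without a baseline or fellow-eye covariate?** Yes. In 20,000 simulated trials with 46 per arm and no true effect, a prognostic baseline factor was left out of the analysis. The mean difference was -0.001 SD when the factor correlated 0.5 with the outcome, and -0.0004 SD at 0.7. Type I error was 4.7% and 5.0%. Chance imbalance in such a factor has SD √(2/46) = 0.21 of its own SD, and the confidence interval already allows for it.

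**2. What precision does fellow-eye acuity offer?** If it explains a share R² of the residual score variance, the standard error falls by 1 - √(1 - R²):

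- R² = 0.20: 1 - √0.80 = 10.6%
- R² = 0.40: 1 - √0.60 = 22.5%

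R² here means variance left after age and preoperative vision. If preoperative vision already covers both eyes, part or all of this gain is already in the plan.

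**3. How much could dilution matter?** Suppose the techniques differ by d = 0.5 SD in their effect on the operated eye, and a fraction k of that reaches the person-level score. Power ≈ Φ(k·d / √(2/46) - 1.96), with √(2/46) = 0.2085:

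- k = 1: Φ(2.398 - 1.96) = 67%
- k = 0.5: Φ(1.199 - 1.96) = 22%
- k = 0.25: Φ(0.600 - 1.96) = 9%

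Covariate adjustment reduces the noise but does not restore the diluted effect.

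**4. What would support comparable scores?** The unadjusted 95% confidence interval half-width is 1.96 × SD × √(2/46) = 0.409 SD. That is 4.1, 6.1 or 8.2 points for SD 10, 15 or 20. A nonsignificant t test is therefore compatible with true differences of several points.

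With a margin m and one-sided 0.025, noninferiority power at a true difference of zero is Φ(m / SE - 1.96). For SD 15, SE = 15 × 0.2085 = 3.13:

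| Margin | No covariate | Covariate correlated 0.5 with the score (SE = 3.13 × √0.75 = 2.71) |
|---|---|---|
| 5 points | 35.9% | 45.5% |
| 10 points | 89.2% | 95.8% |

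The choice of margin decides whether the question can be answered. A covariate helps but does not replace it.

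**The case against.** The strongest reply is that a randomized comparison at one time point needs neither a baseline nor the fellow eye. That is correct. A reader might infer that leaving them out biases the comparison, or that a chance imbalance in fellow-eye vision would pass for a technique effect. The documents do not support either reading: allocation is randomized 1:1, and step 1 shows no bias and the intended error rate.

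A reader might also infer that comparable scores cannot be concluded because the baseline is missing. That link is wrong. The main obstacle is a difference test with no margin. A baseline without a margin would leave it in place, while a 10-point margin at SD 15 could be tested without a baseline.

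It can be said too that the article is condensed and never states that only the study eye is measured. This stands: neither the preoperative acuity nor the covariate names an eye, so one cannot say that fellow-eye vision goes unrecorded. Several exclusions, such as retinal disease and advanced glaucoma, are not limited to the operated eye and may narrow fellow-eye disease. Fellow-eye lens status is still unrestricted.

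The documents do not describe the questionnaire's items or scoring. The labelling point rests on its name, and the person-level point on who answers it. Outcome Measures and the Discussion do mention visual function beside satisfaction, so the function construct is not hidden. The article nevertheless states a satisfaction hypothesis and names nothing else to test it with. Table 1 lists patient comfort at Day 30, but with no instrument, and it is not among the outcomes.

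Finally, Day 90 fellow-eye acuity would be a poor main covariate. It is measured after randomization, patients and surgeons are unblinded, and nothing shown rules out fellow-eye surgery before Day 90 that depends on how the study eye fared. This objection stands and shapes the fix.

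**Conclusion.** The point holds as a cheap improvement to a secondary outcome. The primary outcomes are untouched.

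- **Label:** firm from the text. The only instrument is named for visual function, and satisfaction is what the hypothesis, the abstract and Table 1 claim.
- **Sensitivity and precision:** a loss, not a flaw in validity. Adjusting for fellow-eye acuity would cut the standard error by about 11% to 23% if it explains 20% to 40% of residual score variance. That range is assumed, and the gain shrinks if the planned covariate already includes the fellow eye. The fall in power from 67% to 22% or 9% likewise rests on assumed transmission fractions of one half and one quarter.
- **Comparable scores:** not supportable from a nonsignificant t test without a margin, whatever covariates are used.

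The stronger conclusion, that the questionnaire comparison is invalid or confounded by the fellow eye, does not follow.

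**What to change.** 1. In the abstract, Hypothesis, Table 1 and Outcome Measures, name the NEI VFQ-25 outcome vision-related function. Either drop the satisfaction claim, or add one study-eye satisfaction item at Day 90 and base any satisfaction statement on that item alone.
2. Record preoperative fellow-eye acuity and lens status, and add preoperative fellow-eye acuity as a named covariate in the NEI VFQ-25 comparison. State which eye preoperative vision refers to. Use Day 90 fellow-eye status only descriptively or in a sensitivity analysis.
3. Replace the expectation of comparable scores with the adjusted difference and its 95% confidence interval, unless a margin is prespecified.

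**Cost:** one extra data field, one optional question and a narrower claim about satisfaction. Enrollment was under way at submission. The renaming and the reporting rule can still be set before analysis, but for patients already operated the fellow-eye value would have to come from existing records, if it is there.

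A preoperative NEI VFQ-25 is not required. It would narrow the interval by 1 - √(1 - r²), that is 13% at r = 0.5 and 29% at r = 0.7 (assumed correlations). However, eligibility is confirmed only during surgery, so every consenting cataract patient would have to complete it.
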